### Sample size

Data from Fuchs and Fuchs [28] and Wickes [29] were used for the population estimates. In this first meta-analysis the effects of examiner familiarity on children’s test performance was examined. The data for the meta-analysis came from 22 controlled studies involving 1489 subjects. In the typical study, the effect of examiner familiarity raised test performance by .28 standard deviations. Differential performance favoring the familiar examiner condition was greater when subjects were of low socioeconomic status (SES), were tested on comparatively difficult tests, and knew the examiner for a relatively long duration. The second study tested the general hypothesis that test results will be modified by those aspects of the testing situation which are sometimes not carefully controlled or are treated as if they were unimportant. Thirty-six male subjects in two experimental groups and one control group were used to study the effects of perfunctory verbal comments and nonverbal actions on test results. The findings of the study suggest that such comments as ‘Good’ or ‘Fine’ and such actions as smiling and nodding by examiners have a decided effect upon test results. These data is used as population estimates when comparing the effect of active coaching and personalized feedback versus general non-personalized coaching in Cogmed RM WMT. With a sample size of 50 participants (25 per group), our trial will have 79% power to find an effectsize of .40 between groups and a power of 93% to find an effectsize of .50, when co-variating for WM performance at baseline level. An unpublished study in a similar patient group ([name], [name], [name], [name]. Working memory training in children with neuropsychiatric disorders and borderline intellectual fucntioning; a randomized controlled trial, unpublished raw data) has shown that four (5%) out 76 participants dropped out of the study. Therefore we will include 2 extra participants in this second intervention study. In total, 52 participants (26 per group) will be included.

### Statistical analysis

Statistical analyses of all data will be undertaken using the SPSS statistical program (SPSS 21.0). Descriptive statistics will be reported for each variable of interest for the two groups (active coaching versus general non-personalized coaching). First univariate analyses will be carried out. An independent-samples t-test will be run to determine if there are differences in age, IQ or severity of ADHD or ASD symptoms (measured with the VISK or AVL questionnaire) between the two groups. A chi-square test will be used to examine whether there is an association between gender, use of medication, whether the intervention occurred in a subject’s home or school and the group (active coaching versus general non-personalized coaching).

The mean, standard error (SE) and 95% confidence intervals will be computed for each parameter. For the primary analyses, an analysis-of-variance (ANOVA) will be conducted on the backward block recall task with group (2 levels) as the between-subject factor and time (pre-, post and follow-up assessment) as the within-subject factor. The group by time interaction will show the treatment effect (*p < 0.05).* For the secondary analyses, a multivariate ANOVA (MANOVA) will be conducted on the other neurocognitive, academic and behavioral scales with again group (2 levels) as the between-subject factor and time (pre, post and follow-up assessment) as the within-subject factor. The group by time interaction will reveal the treatment effect on these variables (*p < 0.05).* In case of withdrawal, discontinuation or missing data (if patients have been missed for any reason (i.e. illness) more than 5 training sessions), intention to treat analyses will be performed.

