### Aims

The overall purpose of the study is to gain insight into Cogmed WMT, and in particular to identify which elements may help to develop individually tailored effective treatment possibilities for groups of vulnerable children.

The primary aim of this study is to investigate the efficacy of a less intensive but prolonged Cogmed RM WMT with active personalized coaching and feedback in children with MBID and neuropsychiatric disorders, compared to a less intensive but prolonged RM Cogmed WMT without personalized (i.e. only general non-personalized) coaching and feedback, on neurocognitive functioning as measured with the backward block recall task.Secondly, the efficacy of active personalized coaching will be investigated on various other neurocognitive functioning domains (WM and executive functioning), academic achievements (arithmetic and reading), behavioral problems and parenting style.

It is hypothesized that participants who receive a less intensive but prolonged RM Cogmed WMT with active personalized coaching and feedback demonstrate greater improvement on neurocognitive functioning, academic achievements, behavioral problems and parenting style, directly after training and 6-months post baseline, compared to those who receive a less intensive but prolonged RM Cogmed WMT with only general non-personalized coaching and feedback.

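### The stated 79%/93% power belongs to a baseline-covariate group comparison, but the primary test is a 2-df group-by-time interaction that isolates neither hypothesised time point

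*Protocol article*

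**What the plan says.** The Sample size section claims: "With a sample size of 50 participants (25 per group), our trial will have 79% power to find an effectsize of .40 between groups". For the larger effect size, .50, its figure is 93%. It describes the calculation as made "when co-variating for WM performance at baseline level". The model behind these figures is thus a between-group comparison with baseline working memory as a covariate. The section gives no baseline–outcome correlation and does not say which effect-size metric it uses.

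The Statistical analysis section sets the primary analysis of backward block recall as an ANOVA with group (two levels) between subjects and time (three levels, baseline included) within subjects. It names no covariate. The decision rule is "The group by time interaction will show the treatment effect", at p < 0.05.

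The Aims section hypothesises that children given personalised coaching will "demonstrate greater improvement on neurocognitive functioning, academic achievements, behavioral problems and parenting style, directly after training", and again at the six-month visit. No primary time point or time-specific contrast is named. Below, T1 is baseline, T2 directly after treatment and T3 follow-up, as in Table 1.

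**The concern.** The two sections describe different tests. The first is a 1-df group effect with baseline as covariate. The second is a 2-df interaction with baseline as one of three outcome levels. A reader who takes 79% or 93% as the chance of a significant primary result is relying on a number calculated for another analysis.

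The interaction also gives one p-value for any difference between the two time profiles. The clinical questions are whether personalised coaching helps at T2 and whether it helps at T3. A significant interaction answers neither separately, so the time point that carries the main conclusion could be picked after the result is known.

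Both points come from what the article states, namely a sizing model and a primary decision rule. They do not depend on detail left to a fuller plan.

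**Working it through.** **Inputs from the article.** 25 analysed per group (N = 50); effect sizes .40 and .50; stated power 79% and 93%; alpha .05; three visits.

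**Assumptions, because the article gives no values.** Equal variances, an equal correlation ρ between all visits, and two-sided tests. ρ and the effect pattern over time are varied.

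**Step 1: reproduce the stated power.** For a one-covariate ANCOVA (df 1, 47):
- Effect size read as Cohen's f: noncentrality λ = N·f². For .40, λ = 50 × .16 = 8.0 and power is 79.1%. For .50, λ = 50 × .25 = 12.5 and power is 93.4%. Both match. These values of f correspond to standardised mean differences d of 0.80 and 1.00.
- Effect size read as d: unadjusted t-test power is 28% and 41%. With λ = (n/2)·d²/(1−ρ²), 79% and 93% are reached only with ρ of about .865, which is not stated.

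Under either reading the figures belong to a 1-df test adjusted for baseline.

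**Step 2: power of the stated primary test.** For the interaction, λ = (n/2)·Σ(δₜ − δ̄)²/(1−ρ), df 2 and 96, where δₜ is the group difference at visit t and δ at T1 is 0. The comparators, each on df 1 and 47, are the adjusted T2 contrast, λ = (n/2)·d²/(1−ρ²), and the adjusted mean of T2 and T3, λ = (n/2)·d²/[(1+ρ)/2 − ρ²], where d is then the average of the two effects.

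Worked case, ρ = .6 and differences (0, .50, .50):
- Interaction: Σ(δₜ − δ̄)² = .1667; λ = 12.5 × .1667/.4 = 5.21; power 51%.
- Adjusted T2: λ = 12.5 × .25/.64 = 4.88; power 58%.
- Adjusted mean of T2 and T3: λ = 12.5 × .25/.44 = 7.10; power 74%.

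| Differences at T2, T3 (SD) | ρ | Interaction | Adjusted T2 |
|---|---|---|---|
| .50, .50 | .6 | 51% | 58% |
| .50, .25 | .6 | 40% | 58% |
| .50, .25 | .5 | 32% | 52% |
| .25, .50 | .6 | 40% | 19% |
| .25, .50 | .5 | 32% | 17% |
| .40, .40 | .865 | 80% | 79% |
| .40, .20 | .86 | 65% | 77% |
| .80, .80 | 0 | 52% | 79% |
| .80, .80 | .5 | 83% | 89% |
| .80, .80 | .6 | 91% | 93% |
| .80, .80 | .7 | 97% | 97% |

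The dependence on ρ has a simple form. For a sustained effect, dividing the two expressions for λ gives interaction/adjusted T2 = (2/3)(1+ρ). At ρ = .5 the ratio is 1, so the interaction has the same noncentrality but spends two degrees of freedom. At higher ρ the ratio exceeds 1 and offsets that cost.

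**Step 3: what the interaction separates.** At ρ = .6 the profiles (0, .5, .5), (0, .5, 0) and (0, 0, −.5) all give Σ(δₜ − δ̄)² = .1667, so all have 51% power. The omnibus F treats a lasting benefit, a benefit gone by T3 and a late disadvantage alike.

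**The case against.** A reader might infer that the primary test ignores baseline. It does not. Baseline is a level of the time factor, so the interaction compares changes from baseline, and the hypothesis concerns improvement. What is missing is baseline as a covariate.

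A reader might also infer that neither hypothesised time point is tested. Under randomisation the expected baseline difference is zero, so the interaction null holds only if the arms are equal at both T2 and T3. It is a valid joint test of the two at one alpha. The fair criticism is that it does not isolate either.

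Lack of direction does not count against it specially, since a two-sided adjusted contrast can also be significant in the wrong direction. The article promises means, standard errors and 95% confidence intervals, so the profile will be visible, and follow-up contrasts may be set out in a fuller plan.

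Nor is a power loss established in general. On the plan's own planning values, the interaction roughly equals adjusted T2 if .40 is d with ρ about .865 and the effect lasts. It is close behind if .40 is f and ρ is .6 or more. If the effect grows by T3, a T2 contrast does much worse than the interaction.

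All of this stands. It limits the wording and the size. It does not remove the mismatch between the two sections or the absence of a contrast tied to a hypothesised time point.

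**Conclusion.** The point holds in this form: the power in the Sample size section was not calculated for the test in the Statistical analysis section, and that test does not isolate the effect at T2 or at T3. Both statements hold at any correlation.

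The consequence for power is conditional on equal variances, equal between-visit correlations and an assumed effect pattern. At ρ = .6 with 0.50 SD at both visits, the interaction is 7 points below adjusted T2 and 23 points below the adjusted mean (51%, 58%, 74%). If the effect halves by T3, the gap to adjusted T2 is 18 points (40% against 58%). With a sustained effect it vanishes near ρ = .865. If the effect grows from .25 to .50, it reverses by 21 points (40% against 19%). The documents do not support saying that the planned test always loses power, that it is invalid, or that T2 must be the primary time point.

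**What to change.** 1. Make the primary analysis a model of backward block recall at T2 and T3, with the T1 score as covariate and group, visit and group-by-visit as terms (a linear mixed model, available in SPSS).
2. Prespecify one primary baseline-adjusted group contrast: T2, T3 or their mean. The sponsor should choose it before unblinding, according to which effect matters most and how it is expected to develop. Any other time point should be tested under a stated multiplicity rule, and each contrast reported with its 95% CI.
3. Restate the power for that contrast, naming the effect-size metric (f or d) and the assumed correlation.

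If T3 enters the primary contrast, its date also needs reconciling: the Aims section counts six months from baseline, the Design section from the last session.

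The cost is a change to the analysis and sample-size text. No extra visit, measure or software is needed, and the primary analysis would then match the sponsor's own sizing model. The downside is that the omnibus pattern test is no longer primary and the sponsor must commit to one contrast, which loses power if the effect turns out to lie mainly at another visit.

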### Inclusion and exclusion criteria

#### Inclusion

Children participating in this study will be aged between 10 years 0 months and 13 years 11 months with an IQ score between 60 and 85 (mild to borderline intelligence level). They will have been classified with a neuropsychiatric disorder, i.e. ADHD and/or ASD in line with DSM-IV/DSM-5 [13, 14]. Children with comorbid Oppositional Defiant Disorder (ODD) will also be included. Access to a PC with Windows Vista or Windows XP with an internet connection and speakers at home or at school will be required for the training. Children on medication will only be included if there is “room for improvement of the ADHD symptoms” and medication dosages remain stable during study participation.

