## Discussion

It is of great importance to undertake a treatment-efficacy study in this large vulnerable population of children with MBID and co-occurring psychiatric disorders. Evidence-based treatment possibilities are scarce for these children, since they are often excluded from participation in scientific research due to the heterogeneity of the population. If a less intensive but more prolonged version of the Cogmed WMT intervention with active coaching and feedback appears to improve neurocognitive functioning, academic achievements and/or behavioral problems, it can be implemented in mental health care and special education schools as an evidence-based intervention for children with MBID and neuropsychiatric disorders. Our study also adds to the literature in that this will be the first study to compare effects of different types of coaching. This aspect is of great value, since several studies have shown significant improvements on both the WM condition as well as the placebo condition if coaching is not personalized. Furthermore, a less intensive and more prolonged WMT would probably better fit these children and might result in an increased training benefit and less dropout. On the other hand one could argue that 4 training sessions a week, for a period of 8 weeks, with a shorter duration of training time a day, is indeed less intensive than 5 training sessions a week, for a period of 5 weeks, with a longer duration of training time a day.

Finally, one strength of this study is the double-blind randomized controlled design, which is the most robust design in trials attempting to establish efficacy. This design not only takes into account near transfer effects, but also far transfer effects. These effects are measured up to 6 months after training.

In this study, the second (non-personalized) coaching condition might be a challenge in clinical practice. Coaches should not be tempted to give any substantive feedback to the parent on how to motivate their child when training difficulties occur. On the other hand, a greater degree of training dropout might take place when non-personalized coaching is performed more rigidly. One limitation of this study is the use of single tasks to assess the generalization effects of WMT. It remains unclear whether any improved performance will be due to an acquired underlying ability and/or reflect practice effects. Therefore the results may have to be interpreted cautiously.

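### Intention-to-treat is conditional and tied to missed training sessions, and the named three-visit ANOVA cannot by itself keep children who lack a score

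*Protocol article*

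**What the plan says.** Three parts of the protocol article bear on this.

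- **Statistical analysis, model.** The primary analysis, to be run in SPSS 21, is an ANOVA of backward block recall with group as the between-subject factor and the three assessments as the within-subject factor. The group-by-time interaction at the 5% level is the treatment effect. The secondary scales get a MANOVA of the same shape.
- **Statistical analysis, last sentence.** It lists withdrawal, discontinuation and missing data as the occasions for intention-to-treat. A bracket explains missing data as having missed "more than 5 training sessions), intention to treat analyses will be performed".
- **Sample size and Discussion.** Planning loss rests on an earlier study that "has shown that four (5%) out 76 participants dropped out of the study", and so "In total, 52 participants (26 per group) will be included". The Discussion adds that "a greater degree of training dropout might take place when non-personalized coaching is performed more rigidly".

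**The concern.** Intention-to-treat should be the standing rule for who is analysed and in which arm. Here it is a contingency, and one of its triggers confuses two different things. A child who misses six sessions may have all three recall scores; a child who attends every session may have no follow-up score. The sentence gives a rule that fits the first child and none that fits the second.

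The model adds to the difficulty. A classical repeated-measures ANOVA uses only children with a score at every visit, so a child without follow-up also loses the baseline and post-training scores. The MANOVA has the same need across many scales. Unless something is done beforehand, the children compared are those who stayed. If children who gain little leave the general-coaching arm more often, that arm's average gain is inflated and a real benefit of personalized coaching can be hidden.

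**Working it through.** **1. Plan's own figures.** The protocol states "With a sample size of 50 participants (25 per group), our trial will have 79% power to find an effectsize of .40 between groups"; for 0.50 it gives 93%, with adjustment for baseline working memory. Reading the effect size as Cohen's f, with two groups, one covariate and alpha 0.05, power comes from the noncentral F distribution with 1 and N − 3 degrees of freedom and λ = N·f².

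- f = 0.40: λ = 50 × 0.16 = 8.0, power 79.1%.
- f = 0.50: λ = 50 × 0.25 = 12.5, power 93.4%.

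Both reproduce. Planned loss is 4/76 = 5.3%. Keeping 50 would need 50/(1 − 0.053) = 52.8, that is 53 against the stated 52, which is close enough. From 52, about 52 × (1 − 0.053) = 49 complete children remain.

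**2. Power if incomplete children are deleted** (same formula; loss rates above 5.3% are assumed):

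| Loss | Complete | f = 0.40 | f = 0.50 |
|---|---|---|---|
| 5.3% | 49 | 78% | 93% |
| 15% | 44 | 74% | 90% |
| 20% | 42 | 72% | 89% |
| 30% | 36 | 64% | 83% |

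At the planned loss the cost is about one point.

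**3. Bias if loss is uneven and follows poor gain.** Assumptions, none from the protocol: 26 per arm, three normal scores with unit SD and correlation 0.7 between visits, and no true effect. The chance of loss rises as the pre-to-follow-up gain falls (a latent score equal to minus the standardised gain plus independent standard normal noise). Lost children are deleted from all visits. There were 4,000 simulated trials per row.

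| Loss, personalized vs general | Rejection rate | Bias in pre-to-follow-up change |
|---|---|---|
| 5% vs 5% | 4.9% | none |
| 5% vs 15% | 7.1% | −0.09 SD |
| 5% vs 25% | 9.5% | −0.18 SD |
| 5% vs 35% | 14% | −0.25 SD |

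A negative sign disfavours personalized coaching. Simulation error on a 5% rate is about 1.96 × √(0.05 × 0.95/4,000) = 0.7 points. With the same uneven losses unrelated to outcome, rejection stays at 4.8 to 5.0% and the bias is nil.

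For scale, the examiner-familiarity meta-analysis cited in the Sample size section gives 0.28 SD. A bias of 0.18 SD is 0.18/0.28 = 64% of that.

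**4. A milder mechanism.** Suppose instead that follow-up is lost in one arm according to the post-training score (logistic, log-odds slope 1 to 2 per SD, same correlation). At 20% loss the completers' pre-to-post change is biased by 0.05 to 0.08 SD, and pre-to-follow-up change is not biased. The standard error of the between-arm difference in change is √(2 × (1 − 0.7) × (1/26 + 1/21)) = 0.23 SD. The bias is therefore at most about a third of one standard error, and rejection is about 5.6%. At 5.3% loss in one arm the bias is 0.014 to 0.024 SD and rejection is 5.2 to 5.3%, which is within simulation error of nominal.

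**The case against.** Several points on the other side stand.

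- **The trigger is wider than missed sessions.** A reader who starts at the bracket might infer that intention-to-treat applies to them alone. Withdrawal and discontinuation are listed as triggers in their own right, and the likely intent is to retain such children.
- **A completers-only analysis is not stated.** A reader might infer it from the model and from the usual listwise deletion. The article promises intention-to-treat, and imputation before the ANOVA would be compatible with its text and could sit in a fuller plan that is not shown. What remains is that the two statements do not fit together as written.
- **Uneven dropout is not predicted.** The Discussion says it might happen, on condition that the general coaching is applied rigidly. It gives no rate, and it speaks of leaving training, which is not the same as missing an assessment. It also hopes that the lighter schedule will reduce dropout. The only planning figure is 5% overall.
- **Medication changes remove nobody from the analysis.** A reader might infer post-randomisation exclusion from the inclusion criterion that "medication dosages remain stable during study participation". It is an entry criterion. Neither the Statistical analysis section nor the listed withdrawal reasons exclude a child for a dosage change.
- **A mixed model is not the only remedy.** Multiple imputation would also honour the promise.

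None of this repairs the definition. Treating missed sessions as missing data is an error in the text, which a later analysis plan would have to correct and could not merely fill in.

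**Conclusion.** The point holds in this form: intention-to-treat is conditional, missing data is equated with non-adherence, and the named model cannot alone analyse every randomised child.

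Its size depends on how much is lost and why. Near the planned 5% it is small. It becomes material only when three assumptions hold together: loss well above plan, loss uneven between arms, and loss related to gain. Then the distortion runs against personalized coaching, by about 0.09 to 0.25 SD at 15 to 35% loss in the general-coaching arm. Those rates, the 0.7 correlation and the strength of the link to gain are illustrative and do not come from the protocol. Uneven loss unrelated to outcome costs power but does not bias the test.

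**What to change.** Replace the last sentence of the Statistical analysis section with wording such as: *The primary analysis includes all randomised children in their allocated group, regardless of the number of sessions completed. It uses a likelihood-based mixed model for repeated measures with all available visits. Post-training and follow-up assessments are sought from children who stop training but have not withdrawn consent. An analysis of children who missed no more than 5 sessions is supportive only.* This model replaces the repeated-measures ANOVA; multiple imputation before the ANOVA is an acceptable alternative. The same rule should cover the secondary scales.

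The mixed model corrects for loss that depends on observed scores, as in step 4. It removes only part of the bias when loss depends on the unseen follow-up score, as in step 3. A brief sensitivity analysis for non-random loss is therefore worth adding, and obtaining the assessments matters more than the choice of model.

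The cost is slightly more analysis work, with a procedure that SPSS already offers, and minor effort to invite children who stopped training. The change should be made before unblinding.
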